### Concealment mechanism {16b}

Once a consenting number of suitable participants per intervention round (*n* = 20) have been recruited, subjects will be randomised into intervention group (IG) and control group (CG). This is done by allocating participants to a sequential ID number. Using the *Random Allocation Software* [82], these ID numbers are allocated either to the intervention group or to the control group. The Random Allocation Software will not release the randomisation code until the patient has been recruited into the trial.

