#### Intervention description {11a}

The nutrition therapy Austrian OA Cuisine is based on the framework of the New Nordic Diet [34] combined with the food-based dietary guidelines of Austria [45], the guidelines for OA [22, 46], the typical Austrian cuisine (based on standard works of Austrian cookbooks [47, 48], initiatives to promote traditional and regional foods [49–52] and the principles of a sustainable diet [31].

The nutrition therapy consists of dietetic group training and individual nutritional counselling and is realised by an experienced dietitian. There are 4 group trainings covering 2 h each during the first 6 weeks of the intervention at the David Institute in Krems and at the University of Applied Sciences St. Pölten. The curriculum contains:

General information concerning OA and its inflammatory characteristicsThe role of nutrition in the development and progression of OA [53]The principles of the Austrian OA Cuisine (e.g. largely plant-based, rich in n-3 fatty acids)The practical implementation in daily life (including a recipe booklet)A tasting of different dishes and practical exercises to increase food literacy (e.g. adapting own recipes) [54]Strategies for self-management, self-motivation, self-control and goal-setting [55]

The concept of the Austrian OA Cuisine provides adequate intake of energy and nutrients for the age group over 51 years [56], which is the age group most affected by OA. Besides, it takes the sustainability aspect into account - e.g. by giving preference to regional and seasonal products. The developed diet meets the recommendations for an anti-inflammatory diet [57].

After the end of group training, a comprehensive individual counselling will be provided once a month until 9 months after the study start, either face to face, by telephone, or virtually (MS Teams). The individual counselling consolidates the knowledge and competences and also monitors and motivates participants to keep implementing the therapeutic diet.

After 9 months of nutrition therapy, a follow-up of 3 months will be implemented. During this time, participants should continue to implement the Austrian OA Cuisine on their own.

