### Sample size {14}

An a priori power calculation was performed using G-Power [78] and establishing an ANOVA (F-test) between two measures and two groups for the primary endpoint, the quality of life subscale of the Knee Injury and Osteoarthritis Outcome Score, demonstrating that 50 participants (25 in each group) are required to reveal differences at the 5% significance level, with 90% power, using large effect size (1.1) as reported by previous studies [79, 80]. A change of 8–10 points is considered the minimally important change (MIC) and the standard deviation is set to 15 [81]. Considering a 20% drop-out ratio, we decided to include 30 participants per group (60 participants in total).

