## Statistical methods

### Statistical methods for primary and secondary outcomes {20a}

In this study, the focus is on the comparison of data collected at the beginning of the study (T0) and at the end of the study (T4; T0 + 12 months). For all statistical tests, the significance level is set at *p* < 0.05 in accordance with scientific standards. Data are analysed using IBM SPSS Statistics 28 or greater. Normal distribution of metric variables is tested with Shapiro–Wilk-Test and Q-Q-diagrams. For interpreting the results correctly, we also conduct a descriptive analysis showing the arithmetic mean and standard deviation of metric outcome parameters for each group. To control for outliers, we also report the minimum and maximum for each group in addition to a supportive graphical analysis. For interval and nominal scaled variables, we conduct a frequency analysis. To compare the effects of an evidence-based training programme (GLA:D®) with and without the nutrition therapy Austrian OA Cuisine, we conduct an analysis of variance (ANOVA) based on a mixed-linear model of repeated measures looking for assessing effects within each group (e.g. between baseline and the other data collection points) and between groups. In case variables are non-normal or non-metric in scale, we use the Friedman Test, respectively [83]. The group variable (intervention group or control group) serves as the independent variable and the observed outcome parameters (see {12}) serve as the dependent variable.

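### The stated model leaves out the round and sex used in randomisation, and correlation within the diet arm's training groups; these bias the standard error in opposite directions

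*Protocol article*

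**What the plan says.** All references are to the protocol article.

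- **Randomisation.** Under Concealment mechanism {16b}, allocation waits until a round is full ("Once a consenting number of suitable participants per intervention round", given as 20), and that round is then split between the two arms. Sequence generation {16a} adds stratification by sex. With 60 participants this implies three rounds.
- **Delivery.** Under Intervention description {11a}, the diet therapy opens with group teaching: "There are 4 group trainings covering 2 h each during the first 6 weeks of the intervention". Only the intervention arm receives it. Monthly individual counselling then runs to month 9. GLA:D exercise is also group-based for six weeks, in both arms, at two sites. Strategies to improve adherence {11c} expects close relationships to form among participants in this phase.
- **Analysis.** Statistical methods {20a} describes a repeated-measures mixed model focused on T0 against T4 (month 12). On the explanatory side it states: "The group variable (intervention group or control group) serves as the independent variable". It names no term for round, sex, site or training group.
- **Sample size.** Sample size {14} reports that "50 participants (25 in each group) are required to reveal differences at the 5% significance level, with 90% power" and mentions no allowance for correlation between participants.

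**The concern.** Two features of the design are absent from the stated analysis, and they act differently.

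The first is the set of factors used in randomisation. Round and sex are balanced between arms by design. If they predict outcome and are left out, their variation stays in the residual, and the standard error of the arm difference comes out larger than it should. The cost is some precision.

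The second is treatment in groups. People taught together may end up more alike than people taught apart. If this happens in groups that belong to one arm, the arm mean is less certain than the independent-observations formula says, and the p-value is too small. A round term does not remove this, because the correlation lies within one arm of a round. With three rounds there are few such groups, so a p-value near 0.05 on the KOOS quality-of-life subscale would be open to this criticism.

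**Working it through.** **The plan's own figure.** Inputs from Sample size {14}: alpha 5% (taken as two-sided), effect size 1.1 (read as a standardised mean difference, since the metric is not stated), 25 per arm. The noncentrality is 1.1 × √(25/2) = 3.89, which gives about 97% power by the t-test. 90% needs 19 per arm. Repeated-measures F-tests with f = 0.55 or 1.1 give totals of 4 to 36. So 50 does not follow from 1.1.

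**Arm-specific training groups.** Assumptions, none from the document: unit variance, 30 per arm, ICC of 0.02, 0.05 or 0.10, clustering in the diet arm only. Group size m is 10 if each round forms one diet group (60/3 rounds/2 arms), or 5 if each round splits evenly across the two sites.

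- Design effect: DE = 1 + (m − 1) × ICC
- True variance of the arm difference: (DE + 1)/30
- Expected sample variance in the clustered arm: V = (30/29) × (1 − DE/30)
- Ratio of true to estimated variance: R = (DE + 1)/(V + 1)
- Real type I error: P(|t with 58 df| > 2.002/√R)

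| m | ICC | DE | V | R | 2.002/√R | Type I error |
|---|---|---|---|---|---|---|
| 5 | 0.02 | 1.08 | 0.997 | 1.041 | 1.96 | 5.5% |
| 5 | 0.05 | 1.20 | 0.993 | 1.104 | 1.91 | 6.2% |
| 5 | 0.10 | 1.40 | 0.986 | 1.208 | 1.82 | 7.4% |
| 10 | 0.02 | 1.18 | 0.994 | 1.093 | 1.91 | 6.1% |
| 10 | 0.05 | 1.45 | 0.984 | 1.235 | 1.80 | 7.7% |
| 10 | 0.10 | 1.90 | 0.969 | 1.473 | 1.65 | 10.5% |

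Simulation with 40,000 trials per cell agrees to within about half a percentage point. If the arms also exercised in separate groups, R = DE/V, and the error would be 5.9%, 7.4% and 9.8% (m = 5) or 7.1%, 10.5% and 15.8% (m = 10).

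**A round effect shared by both arms.** Take 10 per arm per round and let ICC be the share of variance due to round. The shared shift cancels from the arm difference, so R = (1 − ICC)/V. At 0.05 this is 0.95/0.9845 = 0.965, the threshold becomes 2.002/√0.965 = 2.04, and the type I error is 4.6%. Simulation gives 5.0%, 4.6% and 4.4% at 0.02, 0.05 and 0.10. The error is on the conservative side.

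**Power at the stated effect size.** With m = 10 and 25 per arm, SE = √(DE/25 + 1/25) for diet-arm clustering, and power = Φ(1.1/SE − 1.96). This gives 96%, 94% and 90% at ICC 0.02, 0.05 and 0.10. With both arms clustered, SE = √(2 × DE/25), and power is 95%, 90% and 81%.

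**Which random effect reaches the contrast.** In a model of T0 and T4, a training-group intercept that is constant over time adds the same amount at both visits. It therefore cancels from the change, and so from the arm-by-time contrast. A check with group correlation arising only after baseline (3 diet groups of 10, group variance 0.10, 300 trials) gave an interaction SE of 0.262 with or without that intercept. The true value was about 0.32, and rejection was 13% either way.

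**The case against.** The strongest counter-argument is that the correlation may be negligible. Group sessions stop at week 6, later diet counselling is individual, and the main comparison is at month 12, over ten months after the groups end. The article gives no ICC and does not say whether the arms exercise together or how rounds divide between the sites. This stands: the size of the inflation cannot be derived from the document, and the table shows only what assumed values would imply.

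It can also be said that a journal article need not specify a full model. The sentence naming the arm variable does not exclude other terms, and the same section also looks at effects over time. An analysis plan that is not shown could add them. This stands in part. The article does describe how participants are allocated, and then names arm alone as the independent variable. Its 90% power is also fixed without any allowance for correlation.

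Two stronger readings are tempting and are not supported. A reader might take the round of 20 as the cluster and conclude that ignoring it makes standard errors too small. Each round contains both arms, so the effect runs the other way. A reader might also infer that power is overstated. At the stated effect size, 25 per arm gives about 97%, and power stays at about 90% or more for ICCs up to 0.05 even with both arms clustered. That 50 does not follow from 1.1 is a separate matter.

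**Conclusion.** The point holds as an inexpensive improvement to the analysis, of moderate weight. The design randomises within round and by sex and teaches the diet in arm-specific groups, and the stated model reflects none of this. Omitting round and sex costs a little precision. Omitting positive training-group correlation would make the test anti-conservative: about 5.5% to 7% for groups of 5 and 6% to 10% for groups of 10. Those ranges rest on assumed ICCs of 0.02 to 0.10, clustering in the diet arm only, and 30 analysed per arm. They tend to the nominal 5% as the ICC approaches zero, which is plausible at month 12.

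**What to change.** 1. In Statistical methods {20a}, add intervention round and sex as fixed effects. In the repeated-measures model include their interactions with time; in a baseline-adjusted T4 model enter them as covariates. This uses three degrees of freedom (two for three rounds, one for sex).
2. Record each participant's training group (site by round by arm) now, since it may be hard to reconstruct later. State whether the arms exercise together.
3. Add a sensitivity analysis with partially nested clustering: a training-group effect on the T4 outcome adjusted for baseline, or a training-group-by-time random effect. Use small-sample degrees of freedom such as Satterthwaite, and report the interval beside the primary one. Do not use a random intercept that is constant over time, because it would leave the T0-to-T4 contrast unchanged and give false reassurance.
4. In Sample size {14}, state that the calculation assumes no correlation within training groups.

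The cost is a few lines of model syntax, one recorded variable and one sentence. With so few groups, the sensitivity interval will be wider and imprecisely estimated, which is why it should stand beside the primary analysis and not replace it.

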### Implementation {16c}

The treatment allocation will be performed by one member of the study team. After the participants’ randomisation, group allocation will be communicated via email.

## Assignment of interventions: Blinding

### Who will be blinded {17a}

A blinding of study participants will not be possible because of the obvious differences between the intervention group and the control group. Blinding will be implemented for the medical staff and the outcome assessors of the measurements and the following analyses (see ‘Data management {19}’).

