#### Procedure for unblinding if needed {17b}

It is an open-label study and therefore unblinding will not occur.

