## Data collection and management

### Plans for assessment and collection of outcomes {18a}

During the registration process, contact data of all interested individuals are collected. The data are deleted if the person disagrees to participate in the study or does not meet the criteria.

All parameters as described in the subsection ‘Outcomes (see {12})’ are taken in a group testing setting with appropriate COVID-19 safety measures, e.g. testing, vaccination, hygiene procedures by the staff of the St. Pölten University of Applied Sciences either at the university itself or at David Institute Krems.

Due to the need for blood sampling and anthropometric measurements at T0, T2, T3 and T4, data collection is conducted in the morning in a fasting state. Anthropometric measurements are conducted with light clothing and carried out by dietitians and nutritionists.

The functional tests (40 MFPWT and 30 SCST) are also carried out with light and casual clothing as well as shoes after the anthropometric measurements. A fasting state is not necessary. Demographic and anamnestic data as well as quality-of-life parameters (KOOS and EQ-5D-5L) are collected via online questionnaires using LimeSurvey (https://www.limesurvey.org/de) as online survey tool. For the data entry, the participants use prepared laptops at the measurement site. Blood samples are collected by medical staff from the David Institute. Fresh blood samples are centrifuged and processed according to the specifications of each biochemical parameter (see ‘Outcomes {12}’) at the University of Continuing Education Krems (located in close proximity to the David Institute). All processed blood samples are stored at − 80 °C and analysed at the University of Continuing Education Krems and at the University of Vienna.

Besides this data collection at the measurement appointments, 24-h dietary recalls are conducted as described in Outcomes ({12}).

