### Data management {19}

The participants agree that for the purpose and in the course of this study, the St. Pölten University of Applied Sciences collects and processes behavioural, anthropometric, demographic and anamnestic data as well as data from the KOOS and functional tests (see ‘Outcomes {12}’). Furthermore, the participants agree that the University of Continuing Education Krems and the University of Vienna transmit the biochemical data (see ‘Outcomes {12}’) in pseudonymised form to the St. Pölten University of Applied Sciences.

The participants’ data are pseudonymised and assigned a fixed identification code. This code is stored safely in a password-protected file, accessible only by the study coordinator (BW) and central staff members (SC, TA, EH). Thus, it is only possible for persons who are entrusted with the evaluation of the data to infer the identity of the participants.

Data acquisition and data processing are performed using commercial software. All data obtained are stored in computer files in encrypted form at the server of the St. Pölten University of Applied Sciences. The handling of the data complies with the European General Data Protection Regulation, the Austrian Data Protection Act and the recommendations of the Austrian Ethics Committees.

Quantitative data are stored and analysed via the statistical software package SPSS at servers of the St. Pölten University of Applied Sciences. To be able to merge the data from the online questionnaires, anthropometric measurements and the blood sample data, a defined coding system is used. Therefore, central staff members (SC, TA) take part in every measurement and organise the participants and coding system. Hence, every participant gets their identification code for the anthropometric measurements and the blood samples and a personalised link including password for the online questionnaire via *Limesurvey*. The identification code ensures that the study staff do not know to which group each participant belongs. To support participants in completing the online questionnaires, prepared laptops and supporting staff members are available. The questionnaires are checked on site by the study staff in terms of completeness and correctness related to the specifications of the questionnaires. Study data from online questionnaires are exported and saved as a comma-separated values (CSV) file after every measurement.

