### Frequency and plans for auditing trial conduct {23}

The whole consortium meets at least twice a year, depending on the project’s tasks.

The study coordinator (BW) and central staff members (SC, EH, TA) meet twice a month to review the general study conduct. Furthermore, the staff members responsible for the GLA:D® training programme (BW, MF, AH, TA) as well as the staff members responsible for the Austrian OA Cuisine and nutritional counselling (SC, EH, GL) meet twice a month. Moreover, central nutrition-related decisions are supervised by KHW and ON. The Data Monitoring Committee (DMC) meets as described in the subsection ‘Composition of the data monitoring committee, its role and reporting structure {21a}’.

The study coordinator (BW) reports to the Ethics Committee as well as to the funding organisation at least once a year. If adaptations of the study protocol should become necessary, further notifications are made to these organisations by the study coordinator.

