## Data Availability

Only the data monitoring committee (see ‘Composition of the data monitoring committee, its role and reporting structure {21a}’) will have access to the final trial dataset.

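### The blinding claimed for outcome assessors, study staff and analyses cannot hold for all of them under the protocol's own role assignments

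*Protocol article*

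**What the plan says.** The section Who will be blinded {17a} accepts that participants cannot be blinded. It then states "Blinding will be implemented for the medical staff and the outcome assessors of the measurements and the following analyses" and refers to Data management {19}. That section gives the mechanism: "The identification code ensures that the study staff do not know to which group each participant belongs". The section on unblinding {17b} says "It is an open-label study and therefore unblinding will not occur".

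The role assignments stand elsewhere in the protocol article:

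- Data management {19}: four people can open the file linking codes to persons, namely the study coordinator and three central staff members. Two of the central staff "take part in every measurement and organise the participants and coding system". Those who evaluate the data are able to work out identities. Staff are on hand to help with the questionnaires and check them on site.
- Frequency and plans for auditing trial conduct {23}: three people are listed as the "staff members responsible for the Austrian OA Cuisine and nutritional counselling".
- Plans for assessment and collection of outcomes {18a}: anthropometry is "carried out by dietitians and nutritionists". Blood is drawn by medical staff of the David Institute. Participants enter KOOS themselves on laptops.
- Composition of the data monitoring committee {21a} names four members. Data Availability says that only this committee "will have access to the final trial dataset". Confidentiality {27} says more widely that the study staff use the dataset for analyses and publications.
- Concealment mechanism {16b}: "these ID numbers are allocated either to the intervention group or to the control group".

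**The concern.** A code hides the arm only from someone who does not otherwise know it. A person who counsels intervention participants for months knows their arm by sight, whatever number is on the form. If that person is present when outcomes are collected, or analyses the data, the stated blinding fails at that point.

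The exposed steps are those where staff can influence the result: the waist tape measurement, the 40-m walk and 30-s chair stand tests, on-site help with questionnaires, and decisions in the analysis. The last matters here because the plan leaves choices open until the data are seen. The test depends on the distribution found (Statistical methods {20a}), and subgroup analyses depend on the data (Additional analyses {20b}). A reader who takes the blinding statement at face value would rate the risk of bias in these steps too low.

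**Working it through.** No arithmetic model applies. The check is to match the role lists against each other and then test each part of the blinding claim.

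| Role | Section | People | Of these, key holders |
|---|---|---|---|
| Can open the code file | {19}, {27} | 4 | 4 |
| Attend every measurement | {19} | 2 | 2 |
| Responsible for nutritional counselling | {23} | 3 | 2 |
| Data monitoring committee | {21a} | 4 | 4 |

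Overlaps: 1 of the 2 people at every measurement is on the counselling list. The committee and the key holders are the same 4 people, and 2 of these 4 are on the counselling list. The number of committee members without the key is 4 − 4 = 0.

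**Study staff.** Trial design {8} and Intervention description {11a} give the counselling to the intervention group only: four group sessions in the first 6 weeks, then monthly individual contact up to 9 months. Four of the five measurement times (T1 to T4) come after this contact has begun. For the person on both lists, the statement that the code hides the group cannot be true.

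**Outcome assessors.** Anthropometry is assigned to the professions that deliver the diet, and no section says they are different individuals. Weight, height and body fat come from a device; waist is taken by tape. The staff running the walk and chair tests are not named.

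**Following analyses.** The phrase has two readings. If it means the laboratory analyses, nothing contradicts it. If it means the statistical analysis, which the cross-reference to {19} also covers, it does not fit Data Availability: everyone given the final dataset holds the key and half of them have a counselling role. {19} itself says the evaluators can infer identities. No masked dataset is described.

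**Medical staff and laboratories.** Blood is drawn by David Institute staff and analysed at two other universities, which return results under pseudonym. No section gives these people the key or a counselling role.

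**The code file.** It links person to code and is not said to contain the arm. The ID numbers are what is randomised ({16b}), but the article does not say whether these are the same as the identification codes in {19}. The argument for the counselling staff does not depend on this.

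**Primary outcome.** KOOS quality of life is completed by participants who know their arm. Assessor blinding has no bearing on how they answer; the only staff contact is support and checking.

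**The case against.** Several points on the other side are sound.

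- Open-label treatment with blinded assessors is an ordinary design, so {17b} does not in itself contradict {17a}.
- Attending and organising a measurement is not rating it. No section says that either of the two central staff members scores an outcome.
- {23} says responsible for the counselling, in a list of who meets with whom. That this person delivers the sessions is a natural inference, not a statement.
- The on-site questionnaire check concerns whether forms are complete and correctly filled in; it is not scoring.
- {17a} openly says participants are unblinded, so no careful reader is misled about the primary outcome.

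These points narrow the concern but do not remove it. The sentence in {19} is unqualified, and it fails for a person whom the same section places at every measurement.

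Two stronger readings are tempting. A reader might infer that the trial has no blinding at all; the document does not support this, because nothing contradicts blinding of the blood-sampling staff and the laboratories. A reader might also infer that the key holders alone control the final dataset; Data Availability suggests it, but Confidentiality {27} speaks of the study staff, so the two sections disagree and neither settles it.

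**Conclusion.** The blinding claim is contradicted for at least one person present at every measurement. It is unsupported for anthropometry and for the statistical analysis. It stands uncontradicted for blood sampling and laboratory work, and it is irrelevant to how participants answer KOOS.

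The extent can be stated only as counts: 1 of the 2 staff at every measurement is on the counselling list, and all 4 people given the final dataset under Data Availability hold the key, 2 of them with a counselling role. The document gives no basis for a shift in KOOS points or any other outcome, and none is claimed.

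The conclusion assumes that people listed as responsible for counselling know who is counselled. The finding on the analysis also assumes that Data Availability, rather than {27}, describes who analyses. This should be corrected because the plan credits the trial with a protection that its staffing does not give.

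**What to change.** 1. Run the primary analysis on a dataset with arms labelled A and B, by a team member who has neither the key nor a counselling role. A key holder who does not analyse can prepare the export. Leave out variables that exist in one arm only, such as attendance at dietetic sessions. Unmask once the primary output is frozen. No committee member qualifies as analyst, so the access rule in Data Availability must be widened, as {27} already implies.
2. Reconcile {17a}, {19}, {27}, {21a} and Data Availability by stating blinding by role and outcome. Participants, counselling staff and on-site key holders are unblinded. KOOS quality of life is self-reported without blinding. Laboratory work and the masked primary analysis are blinded.
3. At any visits still to come, have existing staff without a counselling role take waist measurements, run the functional tests, and support or check questionnaires.

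The cost is one masked export, a text correction and slightly less flexible staffing on measurement days. Step 3 cannot repair measurements already taken. The abstract puts the end of the intervention in October 2024, so with the 3-month follow-up the last visits would fall around January 2025. Steps 1 and 2 need no new data; step 1 is useful as long as the primary analysis has not been run.
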